#### **h. Time horizon of economic valuation**

The cost study will only cover the period of enrollment of children in the study until the release of the last child in the cohort from treatment. This is currently estimated at a maximum of 3 months of treatment per child spread over several months, i.e. approximately 8 months from July 2021 to February 2022.

#### **i. Expected results**

- a. Average cost per SAM child treated for a child on standard dose and on reduced dose
- b. If a Cost Minimization Analysis then we will obtain a percentage of the total cost of treatment under reduced dose compared to that of children in the control group;
- c. If a Cost Effectiveness Analysis then we will obtain a cost ratio per additional SAM child cured by the reduced dose approach

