## **Research hypotheses**

### **Main hypothesis**

Children receiving the reduced dose will have the same weight gain from admission to discharge as children receiving the standard dose of RUTF with a non-inferiority margin of 0.5g / kg / day.

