### **Secondary assumptions**

- Children receiving the reduced dose of RUTF will have the same performance indicators (cure rate, death, drop-out, relapse) as those receiving the standard dose;
- Children receiving the reduced dose of RUTF will have the same length of stay as those receiving the standard dose;
- Children receiving the reduced dose of RUTF will have the same psychomotor development as those receiving the standard dose;
- Treatment with a reduced dosage of RUTF will be less expensive than treatment with the standard dose.

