## **Annex 5: Economic evaluation**

### **1. Context and rationale**

The present work is a sub-study nested within a clinical trial measuring the effectiveness of the reduced dose of RUTF in the management of SAM without medical complications. The study will take place in the Health Zones (ZS) of Nzaba and Bonzola in the province of Kasai Oriental in the Democratic Republic of Congo (DRC). This province experienced a great conflict between the militia of Kamwina Nsapu and the regular army of the DRC. The consequences of this conflict had very serious influences on the nutritional situation of children under 5 in the province. More than 30% and 33% of them suffer from malnutrition respectively in the ZS of Nzaba and Bonzola.

A cost-effectiveness evaluation in the context of a reduction in the dose of RUTF in the management of SAM children showed that the reduced dosage of RUTF was economically beneficial for the treatment of malnutrition. : the cost of treating a child from admission to discharge in the reduced dosage arm of RUTF was \$ 75 while the cost of treating a child with the standard dosage of RUTF was estimated at \$ 91 for an average length of stay of 8 weeks on both sides (N'Diaye et al, 2021). However, an economic evaluation of the reduced dose has never been evaluated without additional staff to collect the data. A comparative study of reduced dose treatment compared to standard treatment in real conditions presents an opportunity to perform an economic evaluation in parallel. The hypothesis is that this could lead to a reduction in costs per child treated. This is the reason why this evaluation is proposed in the ZS of Nzaba and Bonzola in the province of Kasai Oriental in the DRC.

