##### **c.Type of economic evaluation**

This is a parallel economic evaluation of the clinical trial, based on a static decision tree type model simulating the trajectory of all children with SAM included in the trial. SIf the non-inferiority hypothesis is verified in the DRC context, the type of analysis will be a Cost Minimization Analysis, otherwise it will be a Cost Effectiveness Analysis.

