##### **e.Efficacy data**

The cure rate among all children enrolled in the study, and per arm, will be the main outcome of interest for the economic evaluation. We will explore the cure rate per arm at the end of the 12 weeks maximum treatment, and also we will be able to evaluate the cure rate including the children referred to UNTI who return to UNTA and positively complete their treatment.

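### The cost-effectiveness ratio in Annex 5 is labelled as a cost per additional child cured by the reduced dose, and if that dose is cheaper, as expected, the label fits neither fewer nor more cures

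*Protocol*

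**What the plan says.** Annex 5, section 3.1 c, makes the type of economic analysis depend on the trial result. If non-inferiority is verified, costs alone are compared; if not, "otherwise it will be a Cost Effectiveness Analysis". The main hypothesis sets non-inferiority on weight gain, "with a non-inferiority margin of 0.5g / kg / day".

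Section 3.1 e of the annex chooses a different effect measure for the economic work: "The cure rate among all children enrolled in the study, and per arm, will be the main outcome of interest for the economic evaluation".

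Section 3.1 i, item c, gives the output of the cost-effectiveness branch: "If a Cost Effectiveness Analysis then we will obtain a cost ratio per additional SAM child cured by the reduced dose approach". Item a of the same list gives the average cost per child in each arm. Section 3.2.2 adds total cost by arm, by type of cost and by expenditure item, with a best-case and a less favourable sensitivity analysis.

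On the direction of cost, the secondary hypotheses state: "Treatment with a reduced dosage of RUTF will be less expensive than treatment with the standard dose". Annex 5, section 1, agrees: "The hypothesis is that this could lead to a reduction in costs per child treated". It cites an earlier evaluation with 75 dollars per child on the reduced dose and 91 on the standard dose, with the same average stay of 8 weeks.

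The annex has no rule for lower cost with fewer cures, for the reverse comparison, or for dominance.

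**The concern.** A cost per additional child cured by the reduced dose has its plain meaning only if the reduced dose both costs more and cures more. The protocol expects it to cost less. A positive figure under this label would then come from fewer cures, and a reader would take a saving per lost cure for the price of an extra cure. The figure also moves the wrong way: for a given saving, a larger loss of cures gives a smaller and more attractive ratio.

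Cost savings are a secondary objective and the economic evaluation is to be published, so the meaning of this number matters to those who would use it.

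**Working it through.** **The plan's own figure.** Annex 5 gives no cost-effectiveness ratio to reproduce. The sample size behind the test that selects the branch can be reproduced (section 2.1.6: SD 2.6, margin 0.5, expected difference 0, one-sided 5%, power 80%):

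- Rounded z values: (1.64 + 0.84)² × 2 × 2.6² / 0.5² = 332.6 per arm.
- Unrounded z values: 335 per arm, as stated.

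**Sign check.** Ratio = (cost reduced − cost standard) / (cure reduced − cure standard).

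- Cheaper, fewer cures: positive. It is a saving per cure lost, so the label is wrong.
- Cheaper, more cures: negative. The reduced dose dominates, so no price exists.
- Dearer, fewer cures: negative. The reduced dose is dominated.
- Dearer, more cures: positive. This is the only case that the label describes, and it contradicts the cost hypothesis.
- Equal cures: the ratio is undefined.

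**Illustration.** The cost difference is 75 − 91 = −16 dollars (Annex 5, section 1). The cure differences are assumed, and cost is held constant.

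- −1 point: −16 / −0.01 = +1,600
- −5 points: −16 / −0.05 = +320
- −10 points: −16 / −0.10 = +160
- +2 points: −16 / +0.02 = −800

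**If cost is not constant.** Suppose, as an assumption, that the whole cost rises in proportion to a longer stay when weight gain is slower. At 4.5 against 5 g/kg/day, 75 × 5 / 4.5 = 83.3 dollars. The difference is then 83.3 − 91 = −7.7, and a 5-point loss gives −7.7 / −0.05 = about +153. The saving disappears only below 75 × 5 / 91 = 4.1 g/kg/day.

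**How often the branch is entered.** With a true weight-gain difference of 0, non-inferiority is not shown in about 20% of trials at 335 per arm, 14% at 400 (500 per arm less 20% dropout) and 8% at 500. A trial that fails must show an observed deficit of at least about 0.20 (400 per arm) or 0.23 (500 per arm) g/kg/day.

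**What failure implies for cure.** This was simulated with a bivariate normal for the two arm differences, an assumed 75% cure rate and 400 to 500 per arm. The probability of a lower observed cure rate in the reduced arm, given failure, is:

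- no true cure difference, correlation 0: 50%
- no true difference in cure or weight gain: 69–72% at correlation 0.3, 87–91% at 0.6
- no true cure difference, true weight-gain deficit 0.25, correlation 0.3 to 0.6: 58–69%
- no true cure difference, true weight-gain deficit 0.5, correlation 0.3 to 0.6: 51–52%
- true cure deficit of 5 points: about 95% or more
- true cure gain of 2 points, correlation 0 to 0.3: 23–43%

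The documents give neither the correlation nor a true cure difference, so this range is not a finding about the trial.

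**The case against.** The line in section 3.1 i is one item in a list of expected results, and its wording is the usual generic name for an incremental ratio. Details of sign and dominance are often left to an analysis plan, which may exist and is not shown. This has some force, but the protocol does more than leave the detail open: it names the direction of the comparison, and that direction does not suit the branch in which the ratio is produced.

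The ratio would not stand alone. Cost per child in each arm, cure rate per arm and total cost by arm are all planned, so a careful reader could work out the true meaning. That stands, and it limits the harm.

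A reader might infer that failed non-inferiority most likely means fewer cures, so that the misleading positive ratio is the expected result. The documents do not support that. The test is on weight gain and the ratio is on cure; failing to show non-inferiority is not showing inferiority; and the protocol hypothesises equal cure rates. Under the assumptions above the probability runs from below one half to nearly certain.

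The dollar amounts are also only illustrative. The 16-dollar saving is borrowed from an earlier evaluation with equal stays, while section 3.1 f includes inpatient care and lost productivity, which could rise if fewer children recover. The pattern of a doubled loss halving the ratio depends on constant cost.

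**Conclusion.** The point holds as a defect in the stated output. If the reduced dose is cheaper, as the protocol expects, the label in section 3.1 i, item c, is false for fewer cures and for more cures alike. That conclusion rests on the text and on signs; it needs no assumption about which cure outcome is more likely.

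The size is illustrative: +320 dollars at an assumed 5-point loss and +160 at 10 points, with the cost difference fixed at 16 dollars. How often either case would arise is not established by the documents.

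This is a secondary result in a nested sub-study. The primary endpoint, the sample size and participant safety are not affected. It should still be corrected before analysis, because the number as labelled can be read as the opposite of what it shows.

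**What to change.** Reword Annex 5, section 3.1 i, item c, as follows:

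- Report the incremental cost and the incremental cure rate (reduced minus standard) per randomised child, each with its uncertainty.
- If the reduced dose is cheaper and cures fewer, define the ratio as the extra cost of the standard dose per additional child cured by the standard dose or, equivalently, the saving per cure forgone.
- If one arm is cheaper and cures at least as many, state dominance and give no ratio.
- Keep the present label only for the case where the reduced dose costs more and cures more.

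A cost-effectiveness plane or a net-benefit display is optional; net benefit would also need a value per cure, which the protocol does not give. The change costs a few lines of wording and analysis code. It needs no new data and does not touch the conduct of the trial.

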#### **j. Sample size**

The sample for this study will be made up of all the participants enrolled in the study at the end of the study.

### **3.2.Data collection and analysis**

#### **3.2.1. Data collection methods**

##### **a. Data collection technique**

Data collection will consist of 2 modalities:

- Cost data :
  - Individual interviews with caregivers, caregivers, ACF staff, researchers

- Semi-structured group interviews with parents or legal guardians
- Study efficacy data :

this economic evaluation will use the efficacy study database, which will be made available within 6 months after obtaining the final efficacy results from the main study, i.e. after the final validation of these data by peers (after journal submission, actual review and re-submission of the revised article). The data will be anonymized by the principal investigator prior to data sharing.

## **b. Data collection plan**

### ***Staff recruitment and training***

The collection of cost data will be delegated to existing ACF staff for the reduced dose acceptability sub-study, for which staff will be trained in individual and group interviews.

## **c. Organization of the collection**

The collection of cost data will take place during the enrollment phase of the study, preferably for feasibility issues within health centers.

The collection of efficacy data will take place 1 year later or even later, when the data are validated by the principal investigator.

## **3.2.2. Data analysis**

The estimated unit costs will be used as parameters in a decision tree model simulating the trajectory of all SAM children included in the clinical trial.

The model will follow each child in the cohort from registration to discharge by comparing the two groups. Each event modeled will be associated with its cost in the two treatment strategies in the DRC context.

The total costs of the two interventions compared will be calculated on the basis of the sum of each unit cost calculated for the nutritional follow-up consultation (weekly visits), adjusted to reflect the proportion of individuals who actually benefited from a follow-up visit in each arm of the clinical trial.

Cost data will be cleaned and analyzed using Microsoft Excel 2016 and STATA version 16 software and the decision analysis model will be developed with TreeAge software (TreeAge Pro 2017, Health Care Edition, Williamstown, MA).

The costs will be reported per consultation. The total cost of each arm will be presented globally, by type of cost (direct medical, non-medical, and indirect costs) and by major or

relevant expenditure item (RUTF, drugs, materials, consumables, human resources, communities).

No discount will be applied. Costs expressed in Congolese Francs before being converted into 2021 International Dollars using purchasing power parities.

Sensitivity analyzes will test the model and make it possible to evaluate the results obtained by the reduced dose in the best case and in a less favorable case.

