### c. Strategies to improve protocol adherence

Every evening, the principal investigator, the ACF Research RP and the three data collectors check all the data collected in the field in the different UNTAs. Inconsistencies, outliers or missing information for certain variables are noted and communicated to ACF supervisors who follow up within 24 hours and strengthen the capacities of UNTA agents, and also to RECOs. During their visit to enter data, data entry clerks also communicate certain weaknesses observed to healthcare providers with a view to correcting the data as far as possible.

In some cases where trained providers have moved or left their posts, other providers will be trained by the research team to ensure the continuity of the study.

For each child who does not respond to an appointment, RECO makes a home visit to find out what is going on.

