##### **f. Costs included**

The costs included will relate to prospective costs that may modify the result, i.e. cost of the treated child including the costs of outpatient and inpatient treatment for children who will have complications:

- Direct medical costs (consultation costs for treatment, including drugs, exams, staff time, outreach activities, etc.)
- Direct non-medical costs (implementation time for staff, costs payable by beneficiaries),
- Indirect costs (loss of productivity of beneficiaries corresponding to the time spent receiving the consultation).

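### Annex 5 counts inpatient treatment in the cost per child, but its rule for total arm costs has no term for an inpatient stay

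*Protocol*

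**What the plan says.** **Scope.** Annex 5, 3.1 f (Costs included) covers the "cost of the treated child including the costs of outpatient and inpatient treatment for children who will have complications". Section 3.1 d takes a societal perspective that takes in the health system. Under 2.1.3 a of the main protocol, children sent to the UNTI afterwards return to their own study group, so the cost of a stay belongs to that arm. Annex 8 lists the proportion transferred in each arm as a study variable.

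**Calculation.** Annex 5, 3.2.2 describes a decision tree that tracks each child through treatment. It states: "Each event modeled will be associated with its cost in the two treatment strategies in the DRC context". The events are not listed. The section then gives the one rule for total costs: they rest on the "sum of each unit cost calculated for the nutritional follow-up consultation (weekly visits), adjusted to reflect the proportion of individuals"; the weight is the share of children seen at follow-up, taken arm by arm. It adds that "The costs will be reported per consultation", and its list of expenditure items names nothing inpatient.

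**Use of the result.** Under 3.1 c the evaluation is a cost minimisation if non-inferiority is shown, and otherwise a cost-effectiveness analysis. Non-inferiority is defined on weight gain, with a margin of 0.5 g/kg/day (Main hypothesis). In the cost-minimisation branch the result is a percentage of total cost (3.1 i). The effect measure of the economic evaluation is the cure rate, which may also be computed counting children who went to the UNTI, came back and recovered (3.1 e).

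**The concern.** A UNTI stay is not a weekly outpatient consultation. An analyst who follows the total-cost sentence has nowhere to put it, although 3.1 f says that it is included. The two sections cannot both be applied as written.

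The omission matters if transfers differ by arm. Weight loss, stagnant weight and a failed appetite test are all triggers for transfer in 2.1.3 a, so a dose that works less well could plausibly show itself there. The cost-minimisation branch is the most exposed: it is entered on weight gain alone, and more transfers on the reduced dose would count against the saving only if they stand in the cost total. There is also an asymmetry, because a child who recovers after a UNTI stay can be credited as cured while the stay is not charged.

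Lower treatment cost is a stated secondary hypothesis, so the percentage saving is likely to be quoted.

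**Working it through.** The protocol states no cost result of its own, so there is no figure to reproduce. The check is what the literal rule leaves out.

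**Inputs**
- Cost per child of USD 91 (standard dose) and USD 75 (reduced dose), with an average stay of 8 weeks in both arms, from the earlier evaluation cited in Annex 5, section 1. These figures only set the scale. They are assumed here to be weekly-visit costs alone; the annex does not say whether they contain inpatient care.
- Cost per UNTI stay, C: not in the documents. Assumed USD 50, 100 or 200.
- Transfer rates p0 (standard) and p1 (reduced): not in the documents. Assumed p0 = 10%, and p1 higher by 0, 5 or 10 points. With 500 children per arm (Annex 5, 3.1 b), 5 points is 25 more stays.

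**Visit-only saving**
91 − 75 = USD 16; 16/91 = 17.6%.

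**Saving with inpatient cost included**
Saving = (91 + C·p0) − (75 + C·p1) = 16 − C·(p1 − p0). As a percentage, divide by 91 + C·p0.

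| C (USD) | Equal transfer | +5 points | +10 points |
|---|---|---|---|
| 50 | 16.0 (16.7%) | 13.5 (14.1%) | 11.0 (11.5%) |
| 100 | 16.0 (15.8%) | 11.0 (10.9%) | 6.0 (5.9%) |
| 200 | 16.0 (14.4%) | 6.0 (5.4%) | −4.0 (−3.6%) |

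The literal rule overstates the saving by C·(p1 − p0): from 50 × 0.05 = USD 2.5 to 200 × 0.10 = USD 20 per child. The whole USD 16 disappears at C = 16/0.05 = USD 320 with 5 points more transfers, or at C = 16/0.10 = USD 160 with 10 points more.

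**What the literal rule does capture**
If the reduced dose only prolongs outpatient treatment, the extra weekly visits enter the sum. At 75/8 = USD 9.375 a week:
- 9 weeks against 8: 91 − 84.375 = USD 6.6 (7.3%).
- 10 weeks against 8: 91 − 93.75 = −USD 2.75 (−3.0%).

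**The case against.** The strongest reply is that the annex does not exclude inpatient care. Section 3.1 f includes it expressly, the decision tree attaches a cost to each modelled event, and transfers are recorded by arm. The total-cost sentence can be read as an incomplete description of how visit costs are built up, in a translated text. This stands to the extent that nobody should claim that the sponsor intends to leave UNTI stays out. It does not remove the conflict, because the one sentence that says how totals are formed has no place for them.

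A reader might infer three stronger criticisms. The documents do not support them:
- *That weighting by attendance wrongly books missed visits as savings.* A visit that did not take place cost nothing, so not charging it is correct. An absence does trigger a home visit by a community worker (2.1.3 c: "For each child who does not respond to an appointment, RECO makes a home visit to find out what is going on"), but outreach is among the costs in 3.1 f and communities among the expenditure items in 3.2.2, so that cost may be covered. What remains concerns presentation: attendance of 90% against 95% would move the visit-only saving from 17.6% to (91 × 0.95 − 75 × 0.90)/(91 × 0.95) = 21.9%, and this should not be read as efficiency without default and cure rates beside it.
- *That the rule flatters the reduced dose whenever that dose does worse.* A longer outpatient stay is charged, and equal transfer rates leave the absolute saving unchanged.
- *That the cost sources shut out the UNTI.* The source list reads "Individual interviews with caregivers, caregivers, ACF staff, researchers", where the doubled word may stand for both carers and care providers. The place of collection is "preferably for feasibility issues within health centers", which is a preference. No UNTI source is named, but none is ruled out.

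**Conclusion.** The contradiction between 3.1 f and the total-cost sentence in 3.2.2 of Annex 5 is real and needs reconciling. Followed literally, the rule overstates the saving by the inpatient cost per stay times the excess transfer rate on the reduced dose. This matters most under cost minimisation.

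The size cannot be fixed from the documents. The range of USD 2.5 to 20 per child, against USD 16, rests on assumed stay costs, assumed transfer rates and the reading of USD 91 and 75 as visit costs only. A change of sign appears only in the most extreme cell of the table, and all the percentages are illustrative. The point affects a secondary result; the weight-gain analysis is untouched. It corrects a stated rule, so it is more than detail that could be left to an analysis plan.

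**What to change.** In Annex 5:
1. **3.2.2, total-cost sentence.** State that arm cost = outpatient visits attended, with the RUTF issued + number of UNTI stays × inpatient unit cost + the other costs listed in 3.1 f, divided by the children randomised to that arm. Say that UNTI transfer is one of the modelled events.
2. **3.2.1.** Name a source for the inpatient unit cost, such as UNTI staff or records. Do this now: 3.2.1 c places cost collection in the enrolment phase, and the figure may be hard to recover later.
3. **3.2.2, sensitivity analysis.** Name the transfer rate in each arm as a quantity varied in the best and less favourable cases already planned.
4. **3.1 i.** Show default and cure rates by arm beside the percentage saving.

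The cost is some wording, one extra unit-cost estimate and a count of UNTI stays per arm, with no added patients or procedures. The reported saving may turn out less favourable.

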##### **Secondary objectives**

To assess the effectiveness of a reduced dose of RUTF in the management of SAM in terms of:

- **Duration of edema melting** (in days) since admission.
- **Duration of stay** (in days);
- **Performance indicators (cure rate, dropout, mortality, non-respondent, transfer to hospital)**
- **Treatment cost savings** (average cost and total cost per child treated);
- The growth velocity of anthropometric indices
- **Psychomotor development** children
- **Degree of acceptance** a reduced dose of RUTF by healthcare workers and the community
- **Relapse rate** up to 3 months after the “cured” exit from the program.

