##### b. Additional results

The additional results expected in this study, in the two groups (control and intervention), are:

- **The duration of the edema melting:** calculated in number of days, this indicator corresponds to the time taken for the lower limbs of SAM children to return to their normal volume. The expected result is the onset of melting of the edemas within the first 14 days after admission and their complete disappearance after 21 days of treatment.
- **The length of stay:** calculated in number of days, this indicator corresponds to the time elapsed between admission and discharge ( $PB \geq 12.5\text{cm}$  and / or  $PT \geq -3$  Z score and / or edema melt). The maximum length of stay is 12 weeks or 3 months(12).
- **The cure rate:** A child will be considered cured if he meets the cure criteria according to his admission category: A  $PT \text{ index} \geq -1.5$  or  $PB \geq 125 \text{ mm}$  during two consecutive visits and no edema during two visits (2 consecutive weeks).
- **The dropout rate:** it is the proportion of children confirmed alive who missed two successive visits. The abandonment is confirmed once after the visit of the RECO which confirms that the child is alive despite his 2 absences during the weekly visits. Children who have abandoned will be followed up to 3 months after the abandonment. For children who can be found, offer the caregivers a small snack at the single appointment 3 months after abandonment to take the anthropometric measurements.
- **Death rate :** the proportion of children randomized to the study who died during the intervention at any time.
- **Cost savings** (average cost saved and cost saved per child treated): this involves comparing the cost of treatment for children in care and declared cured in the two groups. We will use a societal perspective including the direct costs of drugs and RUTF

(purchase, transport, transport and storage) to assess the cost for each child, the HR costs involved in the care, the non-medical costs (food and transport. beneficiaries), indirect costs (loss of productivity).

- The growth velocity of the anthropometric variables and indices: it will be a question of evaluating the prevalence of stunting, underweight of the children included in the study in the two groups at the end of the treatment.

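### Annex 5 specifies no sampling interval for the cost saving or the cost-per-cure ratio, and its arm-level method is not reconciled with the main protocol's cost per child and regression rules

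*Protocol*

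**What the plan says.** **Main protocol.** The Secondary assumptions state: "Treatment with a reduced dosage of RUTF will be less expensive than treatment with the standard dose". The Secondary objectives in section 1.2 list cost savings as "average cost and total cost per child treated". Section 2.1.4 b (Additional results) compares treatment cost between groups among children declared cured, and names the resources used "to assess the cost for each child, the HR costs involved in the care". Section 2.3.3 plans linear regression to compare groups on quantitative variables, adjusted and unadjusted, with secondary results by intention to treat.

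**Annex 5.** The evaluation is "based on a static decision tree type model simulating the trajectory of all children with SAM included in the trial" (3.1 c). Section 3.2.2 gives the method: "The estimated unit costs will be used as parameters in a decision tree model". Arm totals are the sum of unit costs of the weekly consultation, "adjusted to reflect the proportion of individuals who actually benefited from a follow-up visit in each arm of the clinical trial". The sensitivity analyses will "make it possible to evaluate the results obtained by the reduced dose in the best case and in a less favorable case".

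If non-inferiority is shown, the output is cost minimisation: "we will obtain a percentage of the total cost of treatment under reduced dose compared to that of children in the control group" (3.1 i). Otherwise it is a cost per additional child cured. The population is all enrolled children, 500 per arm (3.1 b and j).

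**The concern.** A hypothesis that one randomised arm costs less than the other needs a statement of how far chance could have produced the difference. A best case and a less favorable case vary the inputs of a model. They do not describe sampling variation between children. Annex 5 names no confidence interval, bootstrap, probabilistic analysis or test.

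This is more than detail left for later. Annex 5 has its own data analysis section, and the method fixed there aggregates to arm totals before any comparison. Child-to-child variation is lost at that step.

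Two things are at stake. Under cost minimisation, the reader gets a percentage saving with no indication of its precision. Under cost-effectiveness, the reader gets a ratio whose denominator is a difference in cure rates that may be mostly noise.

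The main text adds a second difficulty. It points to a cost for each child, to cured children only, and to regression under intention to treat. Annex 5 uses all enrolled children and arm totals and refers to none of this. Restricting to cured children also conditions on something that happens after randomisation.

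**Working it through.** **The plan's own figures.** No precision or power figure is stated for cost, so there is none to reproduce. The one design calculation (section 2.1.6, 335 per group) concerns weight gain. It reproduces: 2 × 2.6² × (1.64 + 0.84)² / 0.5² = 332.6 with the rounded Z values, and 335 with unrounded ones. It has no bearing on this point.

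**Inputs for the illustration.**
- Mean cost per child: 91 dollars (standard) and 75 dollars (reduced), from the earlier evaluation cited in Annex 5, section 1.
- Children per arm: 500 (Annex 5, 3.1 b).
- Coefficient of variation (CV) of cost per child: not in the documents, so assumed.
- Cure rate: assumed at 75%. Annex 4 says only that outpatient care often exceeds that.

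**Cost difference.** Saving = 91 − 75 = 16 dollars, and 16/91 = 17.6%.

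SE = √{[(91·CV)² + (75·CV)²] / n}; 95% CI = 16 ± 1.96 × SE. Percentage saving = 1 − r with r = 75/91 and delta-method SE = r·CV·√(2/n).

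| Assumed CV | n per arm | SE | 95% CI, dollars | 95% CI, % saving |
|---|---|---|---|---|
| 0.4 | 500 | 2.11 | 11.9 to 20.1 | 13.5 to 21.7 |
| 0.8 | 500 | 4.22 | 7.7 to 24.3 | 9.4 to 25.8 |
| 1.5 | 500 | 7.91 | 0.5 to 31.5 | 2.3 to 32.9 |
| 1.5 | 335 | 9.66 | −2.9 to 34.9 | −1.1 to 36.3 |

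Of these rows, only the last includes zero. It needs both an extreme CV and fewer children than Annex 5 intends to use.

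**Cure difference, the denominator of the ratio.** Half-width = 1.96 × √(2 × 0.75 × 0.25 / 500) = 0.054, or 5.4 points. An observed difference of 2 points would have a 95% interval of −3.4 to 7.4, and one of 3 points −2.4 to 8.4. The interval crosses zero, so the ratio can change sign or become arbitrarily large. The half-width falls to 3 points only when p(1 − p) = 250 × (0.03/1.96)² = 0.0586, that is, at a cure rate of about 94%.

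**What is available per child.** Weekly visits, RUTF distribution and weekly assessment of RUTF consumption are scheduled for each child (Chart 5 and the data collection plan). Annex 8 counts children transferred to hospital. Inpatient days are not listed. Household, staff-time and productivity costs come from individual and group interviews during enrolment (Annex 5, 3.2.1) and are not stated to cover every child.

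**The case against.** The case against is substantial in four places.

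- **Silence is not exclusion.** Annex 5 does not say that the two scenarios are the whole uncertainty analysis, and a separate analysis plan may exist. A reader might infer that the protocol rules out any interval for cost. It does not: section 2.1.4 b (cost for each child) and section 2.3.3 (regression for quantitative variables) can together be read as a between-arm comparison, which would yield one. What stands is that Annex 5, the specific text, does something different and is not linked to those sections.
- **The model is said to follow each child.** Section 3.2.2 does say so, from registration to discharge. But its next paragraph computes totals by arm from attendance proportions, so the statement does not supply a child-level comparison.
- **Data.** A reader might infer that each child's full resource use is recorded. That goes too far. Visits, RUTF and transfers are covered; inpatient days and the interview-based societal costs are not stated to be. The fix has to allow for this.
- **Direction of the saving.** A reader might infer that the saving could be chance. The illustration does not support that at CVs of 40 to 80% with 500 per arm. Chart 2 also cuts weekly sachets from week 3 by between 22% (9 to 7) and 50% (14 to 7), so part of the saving is built in.

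The objection that a tree estimates means, and that means are what matter, is fair as regards the point estimate. It does not supply an interval.

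**Conclusion.** The point holds in a limited form. As written, Annex 5 yields a percentage or a ratio without sampling uncertainty for a stated directional hypothesis. Its population and method also need reconciling with sections 2.1.4 b and 2.3.3.

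The dollar intervals are illustrations. They rest on assumed CVs and on costs from another setting. Under the moderate assumptions the saving remains clearly above zero, so what is missing is its precision: roughly ±4 to ±8 dollars on 16. The gap is more serious for the cost-effectiveness branch, which applies if non-inferiority is not shown. There, at an assumed 75% cure rate, a difference of 2 or 3 points cannot be distinguished from none, and two deterministic scenarios would not reveal it.

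The primary endpoint is unaffected. The change is worth making because a better method than the stated one is available at modest cost.

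**What to change.** In Annex 5, section 3.2.2:

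1. Define a cost for every randomised child: the child's own recorded counts (visits attended, sachets distributed, drugs, transfer to UNTI) multiplied by the estimated unit costs. Use an average unit cost per transfer where inpatient days are not captured, and interview-based averages for household, staff-time and productivity costs.
2. Compare arms as randomised. Report the mean difference and the percentage saving with a 95% CI from a bootstrap stratified by UNTA, since randomisation is within UNTA.
3. If the cost-effectiveness branch applies, bootstrap cost and cure jointly and show the cloud of replicates or an acceptability curve alongside the ratio.
4. Keep the decision tree and the two scenarios as sensitivity analyses, and vary the unit costs there, because resampling children does not cover unit-cost uncertainty.
5. State that all randomised children form the cost population, and align section 2.1.4 b with this. Say whether the regression rule in section 2.3.3 applies to cost.

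**Cost.** Modest extra analysis. Annex 5 already plans Stata and use of the trial database. It should be confirmed before analysis which counts, including inpatient days, are held for each child. The limitation is that the interval reflects only child-level variation in recorded use; averaged components add no spread, and this should be stated with the result.
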